**Figure 2 fig2:**
[figure not shown]
Locations of selected acupoints.

#### Control group

2.8.1

Participants in the control group will receive standardized conventional acupuncture. Sterile single-use needles (0.25 × 25 mm, Jiachen Acupuncture Instruments Co., Ltd., China) will be used at EX-HN1, EX-HN22, HT7, BL62, and KI6, whereas 0.25 × 40 mm (Jiachen Acupuncture Instruments Co., Ltd., China) filiform needles will be used at SP6. Needling depth and angle will be adjusted within a prespecified range according to the anatomical features of each point and the participant’s local tissue thickness. Specifically, EX-HN1 will be inserted obliquely at an angle of 15°–30° along the subgaleal plane, with a target depth of 15–20 mm. At EX-HN22, the needle will be inserted perpendicularly or slightly obliquely to a depth of 10–15 mm, taking care to avoid excessively deep anterior needling. HT7 will be needled perpendicularly to 8–12 mm. BL62 and KI6 will also be inserted perpendicularly, generally to a depth of 8–12 mm. For SP6, perpendicular insertion will be performed to a depth of 25–30 mm. For bilateral acupoints, the right side will be needled first, followed by the left side. After deqi is obtained, needles will be retained for 30 min and removed, with brief compression using sterile gauze when needed.

Deqi will be elicited gently by lifting-thrusting and twirling manipulation after the intended depth is reached. Lifting-thrusting will use an amplitude of about 2–3 mm, and twirling will be kept within 90–180 degrees at approximately 1 Hz for 10 s. Manual stimulation will be applied after insertion and repeated at 10 and 20 min, giving each acupoint about 30 s of planned stimulation per session.

Deqi refers to the characteristic needling response induced by appropriate needle manipulation, including lifting-thrusting and rotation, after achievement of the intended insertion depth (37). Immediately after each manipulation, participants will rate typical needling sensations, including soreness, numbness, distension, heaviness, warmth, and radiating sensation, on a 0–10 numerical rating scale. At the same time, the acupuncturist will evaluate needle-grasp sensation, defined as the pulling, heaviness, tightness, or increased resistance perceived under the needle during manipulation, using a 0–3 scale. For the purpose of procedural standardization, Deqi will be regarded as achieved when at least one typical patient-reported sensation is rated ≥3 and/or the operator-rated needle-grasp score is ≥1 (38, 39).

#### Treatment group

2.8.2

In addition to conventional acupuncture, the treatment group will receive ultrasound-guided SG acupuncture. The pathway was adapted from ultrasound-guided SG block techniques (40–42). Participants will lie supine with the neck slightly extended. A SonoEye V2 musculoskeletal ultrasound system (Wuxi Xiangsheng Medical Technology Co., Ltd., China) with a high-frequency linear probe and sterile single-use needles (0.25 × 40 mm; Jiachen Acupuncture Instruments Co., Ltd., Wujiang, China) will be used. After skin disinfection and sterile probe preparation, the probe will be placed transversely at the C6 level to visualize the carotid artery, internal jugular vein, thyroid gland, trachea, longus colli muscle, and prevertebral fascia. Under real-time in-plane ultrasound guidance, the needle will be advanced along a confirmed safe trajectory toward the prevertebral fascial plane adjacent to the longus colli muscle, while avoiding the carotid sheath, thyroid gland, and tracheoesophageal groove. Needling angle and depth will be individualized by real-time visualization. Gentle manipulation will be limited to 1–2 mm lifting-thrusting, within 90 degrees of rotation, at about 1 Hz for 10 s. Ultrasound-observed soft-tissue micro-movement during manipulation will be recorded as a procedural quality indicator, consistent with evidence that needle-tissue engagement can be quantified (43). The right side will be treated first, followed by the left side (Figures 3A,B); needles will then be retained bilaterally for 30 min without further manipulation.

**Figure 3 fig3:**
[figure not shown]
Ultrasound-guided SG acupuncture. **(A)** Sonographic illustration of SG; **(B)** Ultrasound-guided acupuncture at the SG. SG, stellate ganglion; SCM, sternocleidomastoid muscle; IJV, internal jugular vein; CA, carotid artery; LCM, longus colli muscle.

Before each session, a safety checklist will identify bleeding tendency, anticoagulant use, recent neck trauma, cardiopulmonary instability, or other risk factors. Participants will be instructed to avoid swallowing, coughing, or neck movement during stepwise needle advancement. The procedure will stop immediately if severe pain, electric shock-like sensation, respiratory distress, or loss of continuous needle-tip visualization occurs. Local pressure will be applied after needle removal.

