### Sample size calculation

2.3

This trial has two prespecified primary endpoints: change in Insomnia Severity Index (ISI) score and change in task-evoked prefrontal oxygenated hemoglobin (Oxy-Hb) response measured by fNIRS. A Bonferroni-style alpha-allocation strategy will be used to control the family-wise type I error rate, with a two-sided alpha of 0.025 assigned to each primary endpoint. For the ISI endpoint, a 3-point between-group difference was considered clinically meaningful, consistent with the lower bound of minimal clinically important difference estimates for the ISI (32), and supported by a randomized acupuncture trial in primary insomnia (33). Using a pooled SD of 3.8 from a comparable insomnia population (33), the standardized effect size was estimated as Cohen’s *d* = 3.0/3.8 = 0.79. With a two-sided *α* of 0.025, 1:1 allocation, and 80% power, approximately 32 participants per group are required.

For the fNIRS endpoint, a standardized effect size of *d* = 0.80 was assumed for the between-group difference in prefrontal Oxy-Hb change. With alpha = 0.025, 1:1 allocation, and 80% power, approximately 27 participants per group are required. Because the ISI endpoint requires the larger analyzable sample, it is the binding constraint. After allowing for a 20% attrition rate, the required enrollment sample size was calculated as follows:

$$n_{\text{enrolled}}=\frac{n_{\text{required}}}{1-\text{attrition rate}}=\frac{32}{1-0.20}=40$$

Thus, 40 participants per group, for a total of 80 participants, will be randomized.

Sensitivity analysis showed that, with 32 analyzable participants per group, the study would retain approximately 80.4% power for ISI and 81.4% power for fNIRS Oxy-Hb at alpha = 0.025. If the true fNIRS effect decreases to *d* = 0.75, power would decrease to approximately 75.7%, indicating that the fNIRS endpoint is more sensitive to effect-size assumptions. Strict fNIRS acquisition, preprocessing, and quality-control procedures will therefore be implemented. Previous fNIRS acupuncture studies have generally included 12–20 participants (34–36). On this basis, at least 20 participants per group will be included in the fNIRS analysis. After allowing for an anticipated dropout rate of 20%, 24 healthy controls per group will be planned for fNIRS assessment.

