### Recruitment and procedure

2.5

Recruitment will take place at Tongde Hospital of Zhejiang Province Affiliated to Zhejiang Chinese Medical University through outpatient clinics and online notices distributed via WeChat. Recruitment materials will describe the target population, eligibility criteria, intervention procedures, and contact details. Interested individuals will receive a study brochure and complete a screening form. Eligible patients with CID will then undergo baseline assessment and randomization. Outcome assessments will be conducted at baseline, week 4 (post-treatment), and week 8 (follow-up). Healthy controls will be recruited as a reference group for baseline fNIRS comparison only. Before fNIRS assessment, their eligibility will be verified through clinical interview and baseline assessments.

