#### Eligibility criteria

2.6.2

Participants will be considered eligible for inclusion upon fulfillment of all of the following criteria:

Diagnosis of CID in accordance with the ICSD-3 diagnostic criteria, together with an ISI score of ≥10.Age between 18 and 70 years, with no sex-based restriction, and right-handedness.No use of medications or other therapeutic interventions for insomnia within 1 month prior to enrollment.Preserved ability for normal communication and compliance with study procedures.Written informed consent must be provided.

Healthy controls will be required to meet all of the following criteria:

Right-handed individuals of either sex, aged between 18 and 70 years;An ISI score ≤7, a Pittsburgh Sleep Quality Index (PSQI) score ≤5, and a HAMA score <7;No history of major chronic diseases or severe organic dysfunctions (e.g., cardiovascular, hepatic, or renal diseases);No use of hypnotics, antidepressants, central nervous system stimulants, or any other medications/substances known to substantially affect sleep architecture or central nervous system function within 1 month prior to enrollment;Voluntary provision of written informed consent prior to study participation.

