#### Exclusion criteria

2.6.3

Participants will be excluded upon fulfillment of any of the following criteria:

Presence of severe or unstable medical conditions, including cardiovascular or cerebrovascular disease, malignancy, nephritis, hematological disorders, other life-threatening diseases, or active infectious disease.Presence of severe depressive symptoms, defined as a Hamilton Depression Rating Scale (HAMD) score of >24.Presence of significant impairment in speech, language, or hearing, or the presence of cognitive or neurological disorders.Current substance abuse or severe dependence on alcohol or other psychoactive substances, or current exposure to medications or substances with substantial effects on sleep or central nervous system function, including antidepressants or central stimulants.Presence of secondary insomnia attributable to other organic diseases.Pregnancy or breastfeeding status.History of needle syncope or presence of skin damage at the intended acupuncture sites.Known allergy to metals, including acupuncture needles.Current participation in another clinical study.

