### Randomization and blinding

2.7

Eligible patients with CID will be randomly assigned 1:1 to the treatment or control group. An independent statistician not involved in recruitment, intervention, outcome assessment, or data analysis will generate the randomization sequence. Allocation will be concealed in sequentially numbered, opaque, sealed envelopes. After baseline assessment, a research assistant not involved in outcome assessment or data analysis will open the next envelope and assign the participant.

Treatments will be delivered in separate sessions to reduce contamination. Acupuncturists cannot be blinded because the procedures differ, but participants will not be informed of the study hypothesis or expected superiority of either intervention. Outcome assessors and statisticians will remain blinded throughout the trial. Accidental unblinding will be documented.

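### Anticoagulant use and recent neck trauma are checked before each stellate ganglion (SG) session but are not named entry criteria, so a patient the checklist may flag can already have been allocated to SG needling

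*Protocol article*

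**What the plan says.** The SG procedure is described in section 2.8.2 (Treatment group). The paragraph after Figure 3 sets the safety check: "Before each session, a safety checklist will identify bleeding tendency, anticoagulant use, recent neck trauma, cardiopulmonary instability, or other risk factors". Section 2.8.1, for the control arm, has no counterpart.

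Entry is governed by two lists. Section 2.6.2 opens with "Participants will be considered eligible for inclusion upon fulfillment of all of the following criteria", and section 2.6.3 with "Participants will be excluded upon fulfillment of any of the following criteria". The entries closest to the checklist items are:

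- 2.6.3, medical conditions: "Presence of severe or unstable medical conditions, including cardiovascular or cerebrovascular disease, malignancy, nephritis, hematological disorders", followed by other life-threatening or active infectious disease.
- 2.6.3, needling: "History of needle syncope or presence of skin damage at the intended acupuncture sites", with metal allergy as a separate item.
- 2.6.3, medication: only drugs or substances that act on sleep or the central nervous system.
- 2.6.2, medication: only treatments for insomnia.
- 2.6.2, general: the patient must be able to communicate normally and comply with what the study requires.

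On timing, section 2.5 says "Interested individuals will receive a study brochure and complete a screening form", and Table 1 places a clinical interview and physical examination at week 0. After baseline assessment, section 2.7 has a research assistant who "will open the next envelope and assign the participant".

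**The concern.** The plan recognizes certain patient characteristics as risks of SG needling, but first names two of them at a point that comes after randomization and in one arm only. SG needling is bilateral, directed at the prevertebral plane at C6 beside the carotid sheath, and planned for up to 12 sessions. Entry runs to age 70, so stable patients on anticoagulants are plausible candidates, although the article gives no rate.

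Once such a patient is in the SG arm, there are two possible courses:

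1. SG needling is withheld. Section 2.10 already foresees participants who suspend a component for safety reasons. This can happen only in the SG arm, so it dilutes the contrast that section 3 describes as the add-on effect. If the per-protocol sensitivity set also dropped these patients, similar controls would remain and the two sets would no longer be comparable.
2. SG needling goes ahead at raised bleeding risk. Section 2.10 lists an expanding neck hematoma among its severe events.

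**Working it through.** **Step 1. Set the checklist against the entry lists.**

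| Checklist item (2.8.2) | Nearest entry criterion | Covered before allocation? |
|---|---|---|
| Bleeding tendency | Hematological disorders (2.6.3) | Largely |
| Cardiopulmonary instability | Severe or unstable conditions, including cardiovascular disease (2.6.3) | Largely |
| Anticoagulant use | Both medication criteria concern sleep, insomnia or CNS drugs; the severe or unstable conditions item removes some users | Partly; not a stable patient on an anticoagulant |
| Recent neck trauma | Needling exclusions cover syncope, skin damage and metal allergy | Not by name; skin damage at a needling site only incidentally |

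Two of the four named items therefore lack a named criterion.

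**Step 2. Order of events.** Screening form (2.5), interview and examination (Table 1), baseline assessment, envelope (2.7), then the SG-arm checklist before session 1 and each later session (2.8.2). The two items are first named after allocation, but before any SG needle is placed.

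**Step 3. Reproduce the plan's power figure.** Inputs from section 2.3: ISI difference 3.0, "Using a pooled SD of 3.8 from a comparable insomnia population", two-sided alpha 0.025, 32 analyzable and 40 enrolled per group.

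Power for the two-sample t-test uses df = 2n − 2 and noncentrality (difference/SD) × √(n/2). At n = 32: 3.0/3.8 = 0.789, noncentrality 0.789 × √16 = 3.158, power 80.3%. The article gives 80.4%, so it reproduces to within 0.1 point. The sample size solves to 31.8, hence 32, and 32/0.80 = 40.

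**Step 4. Effect of non-receipt in one arm.** Let f be the share of the SG arm never SG-needled, with no add-on benefit to those patients. The documents give no value for f; every value here is an assumption. The intention-to-treat difference becomes 3.0 × (1 − f), with the SD kept at 3.8.

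For f = 1/40 = 2.5%, the difference is 2.925 and the standardized effect is 2.925/3.8 = 0.770. The noncentrality is 3.079 at n = 32 and 3.442 at n = 40.

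| f (assumed) | Patients of 40 | Difference | Power, 32 per group | Power, 40 per group |
|---|---|---|---|---|
| 0 | 0 | 3.000 | 80.3% | 89.1% |
| 2.5% | 1 | 2.925 | 78.1% | 87.4% |
| 5% | 2 | 2.850 | 75.7% | 85.5% |
| 10% | 4 | 2.700 | 70.6% | 81.2% |

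At 40 per group, power stays at or above 80% until f is about 11%. If 10% of the arm missed just one of 12 sessions and benefit were proportional to sessions, the difference would be 3.0 × (1 − 0.10/12) = 2.975. Power would then be 79.6% at 32 per group and 88.6% at 40, a loss of less than 1 point.

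**The case against.** The strongest reply is that section 2.8.2 calls these items risk factors, not contraindications, and states no rule for withholding. A reader might infer that patients unsuitable for SG needling will be allocated to it. The text does not support that. A risk factor can be managed, and the plan provides real-time imaging that avoids the carotid sheath, stopping rules, pressure after needle removal and at least 30 minutes of observation. If flagged patients are needled under those precautions, there is no non-receipt and no dilution.

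A reader might also infer that the site has no written means of acting at entry. That goes too far. The compliance criterion in 2.6.2 arguably lets an investigator turn away someone known to be unable to undergo SG needling. The interview and examination fall at week 0, the envelope is opened only after baseline assessment, and the content of the screening form is not printed. A third tempting inference, that people are needled unchecked, fails because the checklist precedes session 1 as well as later sessions.

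Further, per-protocol set definitions and the action on a positive item are details an article may leave to fuller documents. In a trial described as a pragmatic add-on comparison, some incomplete receipt is compatible with the aim.

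Most of this stands, and it keeps the point small. What it does not remove is the mismatch between two parts that are both printed. The compliance criterion is a matter of judgement and names neither item. Section 2.6.3 already excludes on needling-specific grounds before allocation, so naming these two items would follow its own approach.

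**Conclusion.** The point holds in a limited form. Anticoagulant use and recent neck trauma are risks to be identified before each SG session but are not named entry criteria. A patient the checklist may flag can therefore be randomized and meet the check only afterwards, in the SG arm. Existing criteria give partial, discretionary cover.

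The consequence is conditional: one-arm non-receipt if SG needling is withheld, or raised bleeding risk if it is not. The intention-to-treat population stays intact either way.

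The size is unknown. One never-needled patient in 40 would cost about 2 points of ISI power, which rests on an assumed share, no add-on benefit without SG needling, and an unchanged SD. At 32 per group any loss takes power below 80%, but only because the design starts at 80.3%. This is an optional, low-cost improvement and not an error that threatens the trial's result.

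**What to change.** Apply the existing 2.8.2 checklist once to every candidate at screening, before the envelope is opened. Add to 2.6.3, for both arms, current anticoagulant use or bleeding tendency and recent neck trauma; the clinical team should settle the exact wording. Keep the per-session SG check for risks that arise later. Follow-up and intention-to-treat retention need no change.

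The cost is one more use of a form that already exists and a short amendment, which section 2.12 requires to go through the ethics committee. The downside is a few more screen failures and slightly narrower generalizability. Moving the check earlier does not by itself reduce needle exposure; it avoids allocating patients to a procedure they may not be able to receive.

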#### Functional near-infrared spectroscopy

2.8.3

fNIRS data will be collected using the BS-7000 system (Wuhan Znion Technology Co., Ltd., Wuhan, China). Healthy controls will undergo baseline fNIRS assessment only, whereas patients with CID will be assessed at baseline, week 4, and week 8. Participants will avoid caffeine for at least 12 h, alcohol for at least 24 h, and strenuous exercise for 1 day before assessment. Recording time, caffeine/alcohol intake, medication use, and overnight sleep duration will be documented. Repeated assessments will be scheduled at similar times of day when feasible (Figure 4).

**Figure 4 fig4:**
[figure not shown]
The positions of the emitters, detectors, and the 49 channels.

After a 5-min seated rest, a flexible cap with 16 sources and 16 detectors will be positioned according to the international 10–20 system, with detector 3 aligned to Fpz. The optode layout will cover frontal, temporal, and parietal cortices, with long-separation source-detector distance of approximately 30 mm. Dual wavelengths of 690 and 830 nm will be used, with manufacturer-preset sampling at 10 Hz. Cap repeatability will be controlled by using the same cap size, recording landmarks and optode positions, taking standardized photographs, and using the same trained operator when possible. Raw light intensity, optode-scalp coupling, and signal-to-noise ratio will be checked before recording.

The protocol will include resting-state recording and a VFT (Figure 5). Before each recording, raw light intensity and optode-scalp coupling will be verified before each recording; channels will be retained only if light intensity falls within the manufacturer-recommended dynamic range and SNR ≥ 30 dB. A 60-s pre-task control period will be conducted under eyes-open conditions, during which participants softly repeat “1-2-3-4-5” to control for speech-related motor activity. The task will consist of two consecutive 30-s blocks, in which participants generate as many words as possible from predefined semantic categories. A 60-s post-task period will follow using the same control articulation. Six familiarity-matched categories (food, animals, household items, occupations, fruits/vegetables, and sports/exercise) will be counterbalanced using a computer-generated Latin-square schedule, so that each patient completes all six categories once across the three assessments. Task onset and duration will be recorded for individual-level generalized linear model (GLM) analysis (Figure 6).

**Figure 5 fig5:**
[figure not shown]
Shows a subject being tested by fNIRS.

**Figure 6 fig6:**
[figure not shown]
Flowchart of the resting-state test and verbal fluency task.

### Outcome measures

2.9

An independent, blinded clinician will perform all outcome assessments. Randomized CID patients will be evaluated at baseline, week 4, and week 8. Healthy controls will only undergo baseline screening and fNIRS, using the ISI, PSQI, and HAMA strictly to confirm eligibility and baseline characteristics. Additionally, self-reported sleep duration (extracted from the PSQI) will be recorded for all participants at baseline, and at weeks 4 and 8 for the randomized group.

#### Primary outcomes

2.9.1

##### ISI

2.9.1.1

The ISI is a validated 7-item scale assessing insomnia severity over the preceding 2 weeks. Items are scored from 0 to 4, yielding a total score of 0–28, with higher scores indicating greater severity. Scores are interpreted as no clinically significant insomnia (0–7), mild insomnia (8–14), moderate insomnia (15–21), and severe insomnia (22–28).

